### Blinding

Researchers involved in data assessments (outcome assessors, study physicians, study psychologists, study psychiatrists, statistician and data collector) are blinded to the patients’ intervention group. The only personnel aware of the treatment groups are the study physiotherapists who randomize the participants to the groups, code them, and also deliver the exercise interventions, but they are not involved in any data analyses. For half of the included patients, participation in low or high intensity training group was double-blind to both study researchers and patients: for the other half of the patients, training intensity group was only blind to the study researchers (the patients were aware of what treatment group they belonged to). Comparison of these two study halves will enable us to determine if blinding procedures reduce result bias. Final unblinding will occur after all assessments are performed and data collected at the 1-year follow-up (June 2021).

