## Methods/design

### Study design

This is a randomized, parallel, controlled superiority clinical intervention study with three assessment points (baseline, post-intervention and one-year follow-up). The study is ongoing and was registered under ClinicalTrial.gov NCT03247270 on August 8, 2017 (https://clinicaltrials.gov/ct2/show/NCT03247270). The protocol was prepared in accordance with the SPIRIT 2013 statement. [29] Participants are randomly assigned to an exercise program of one low-intensity training group, one moderate- to high intensity training group and one control non-exercise group, with 1:1:1 allocation. Assessments and interventions are conducted at Primary Care Rehab (Närhälsan Primary Care) in Gothenburg, Sweden. Figure 1 shows the study design of the trial.

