### Intervention

Using computer generated randomisation (http://www.randomizer.org), patients are randomized into three groups: 1) Intervention I: 12-week exercise program with low-intensity training 3 times per week for 45 min; 2) Intervention II: 12-week exercise program with moderate to high-intensity training 3 times per week for 45 min; 3) Control group: a single physiotherapy session with general advice about physical activity. Participants are then informed by phone if they belong to an intervention group or the control group. Both intervention groups include cardiorespiratory and resistance training, and participants in group II are also encouraged to perform an additional running session per week. Participants in the control group are encouraged to start exercising after the study is completed and also receive a 3-months membership at a training facility, but are discouraged of actuating other exercise programs during the trial. All three groups self-report physical activity during the study. For participants in the intervention groups, the study physiotherapists designed individualized exercise programs during a one-to-one session with the patients on one occasion. The exercise program is designed as a circuit training with 12 stations, repeated twice (45 s workout, 15 s for transportation between stations and 1 min rest between the two laps). It also includes 10 min of warm-up exercises and 5–10 min of cool down and stretching exercises. Cardiorespiratory exercises include step-ups, lunges, jump rope, burpees, step touches side-to-side and step-touches on step board. Resistance training exercises include squats, abdominal plank position, hip lifts, crunches, row exercises and push-ups. Participants in intervention group I and II exercise separately in group sessions in the gym with the physiotherapist according to a predetermined schedule. A pulse-watch and the Borg RPE scale are used to monitor level of exertion to ensure appropriate exercise intensity. For intervention group I, the intensity level corresponds to 1.5–2.9 metabolic equivalents (METs), a Borg rated perceived exertion (RPE) of 10–14 and a maximal heart rate of 40–59%. The corresponding figures for intervention group II are 3.0–8.9 METs, Borg RPE 12–17 and 60–94% of maximal heart rate. Patients who are unable to participate in a session perform replacement exercises on their own.

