### Assessments

Assessments occur at baseline, post-intervention (after 12 weeks) and at one-year follow-up (Table 1). Participants will be assessed by the study physician, psychologist, psychiatrist and physiotherapist.

**Table 1 Tab1:** Measures, methods and assessment points used in the study

Variable	Measure	Method	T0 Baseline	T1 12 weeks	T2 1 year
Psychiatric diagnosis	M.I.N.I.	Interview	X	X	X
Anxiety symptoms	BAI	Self-report	X	X	X
Depression symptoms	MADRS	Self-report	X	X	X
Psychoactive drugs	Questionnaire	Self-report	X	X	X
Blood pressure	MmHg	Objective assessment	X	X	X
BMI	Kg/m^2^	Objective assessment	X	X	X
Alcohol use	AUDIT	Self-report	X	X	X
Quality of life	EQ-5D	Self-report	X	X	X
Cognitive function	WAIS-IV (d.s., b.d., m.r.)	Objective assessment	X	X	X
Cognitive function	D-KEFS (d.f.)	Objective assessment	X	X	X
Cardiovascular fitness	Åstrand’s ergometer test	Objective assessment	X	X	X
Muscle strength	One-leg-rising-test	Objective assessment	X	X	X
Sick leave	Questionnaire	Self-report	X	X	X
Hormones/cytokines	S-IGF-1, S-BDNF, S-VEGF, CRP	Blood samples	X	X	X

*M.I.N.I.* Mini International Neuropsychiatric Interview, *BAI* Beck Anxiety Inventory, *MADRS* Montgomery Åsberg Depression Rating Scale, *BMI* Body mass index, *AUDIT* Alcohol Use Disorders Identification Test, *EQ-5D* EuroQoL-5 Dimension Questionnaire, *WAIS-IV* Wechsler Adult Intelligence Scale, 4th edition, *d.s*. digit span, *b.d*. block design, *m.r.* matrix reasoning, *D-KEFS* Delis-Kaplan Executive Function System, *d.f*. design fluency, *S-IGF-1* serum insulin-like growth factor 1, *S-BDNF* serum brain-derived neurotrophic factor, *S-VEGF* serum vascular endothelial growth factor, *CRP* high sensitivity C-reactive protein

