#### Cardiovascular fitness

Maximal oxygen uptake capacity (VO2max) is estimated using Åstrand’s submaximal ergometer test and serves as a measure of cardiovascular fitness [39]. The test is performed by the physiotherapists at Primary Care Rehab. Participants are told to refrain from vigorous activity the day before the test, to avoid a heavy meal within three hours and smoking/snuff use one hour prior to the test and also to avoid stress during the test day. The ergometer is calibrated for each participant and heart rate is corrected for sex and age. Predicted VO2max is calculated in accordance with the nomogram described by Åstrand and Ryhming [39].

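### Outcome assessors are declared blinded, yet the VO2max test is run by physiotherapists, the role named as aware of allocation

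*Protocol article*

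**What the plan says.** The Blinding section opens with a general claim: "Researchers involved in data assessments (outcome assessors, study physicians, study psychologists, study psychiatrists, statistician and data collector) are blinded to the patients’ intervention group". Physiotherapists are not in that list. The next sentence names them as the exception: "The only personnel aware of the treatment groups are the study physiotherapists who randomize the participants to the groups, code them, and also deliver" (meaning that they also run the training). The same sentence places one limit on them: "but they are not involved in any data analyses".

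Two other sections deal with measurement. Under Assessments: "Participants will be assessed by the study physician, psychologist, psychiatrist and physiotherapist". Under Cardiovascular fitness, about the Åstrand submaximal ergometer test: "The test is performed by the physiotherapists at Primary Care Rehab". Table 1 schedules that test at baseline, 12 weeks and 1 year.

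The Study design section puts testing and training at one place: "Assessments and interventions are conducted at Primary Care Rehab". The Intervention section shows that whoever leads a session knows its intensity: "Participants in intervention group I and II exercise separately in group sessions in the gym with the physiotherapist according to a predetermined schedule".

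The Muscle strength section describes the one-leg rise, including how it must be performed, but does not say who runs or counts it.

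**The concern.** A reader of the Blinding section would take every assessor-measured outcome to be blinded. For estimated VO2max, the other sections point to the one role that the same section describes as unblinded. Being kept out of the analysis does not protect a measurement: a value influenced at the ergometer is already in the data when the blinded statistician receives it.

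Two uses of VO2max are at stake. Physical health is part of the primary aim, and the main hypothesis expects physical health variables to improve. Cardiovascular fitness is also named as a possible mediator or moderator. If testers who know the allocation influence the result, even unintentionally, the fitness contrast between arms is affected, and any analysis that uses fitness to explain the anxiety result inherits the problem. There is also a reporting risk: the trial publication could describe VO2max as a blinded outcome on the strength of this paragraph.

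**Working it through.** No figure in the protocol bears on this point, so the check sets the sections against each other.

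1. **Who is blinded?** Blinding section: outcome assessors, physicians, psychologists, psychiatrists, statistician and data collector.
2. **Who is not?** Same section: the study physiotherapists, and nobody else among the personnel. They carry out the randomisation, do the coding and lead the training. The two exercise groups train separately and the control group gets a single physiotherapy session, so the role has direct knowledge of all three arms.
3. **What are they barred from?** Data analysis. Outcome measurement is not mentioned.
4. **Who measures?** Assessments section: physician, psychologist, psychiatrist and physiotherapist. The first three are in the blinded list of step 1. The fourth is the role in step 2.
5. **Which outcome is tied to the physiotherapist by name?** Only the Åstrand test. Of its three time points, 12 weeks and 1 year fall after randomisation. Baseline is harmless if it precedes randomisation, which I assume because the text does not give the order.
6. **Is a separate blinded testing team described?** No. The term outcome assessors appears in step 1, but nothing links it to the ergometer test.

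Applied to individual outcomes:

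| Outcome | How obtained | Covered by the blinding claim as written? |
|---|---|---|
| BAI | Self-report | Not affected by this conflict |
| M.I.N.I. | Study psychiatrist, listed as blinded | Yes |
| Estimated VO2max | Physiotherapists at the rehabilitation unit | No: contradicted |
| One-leg rises | Tester not named | Cannot be determined |

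Table 1 has 14 rows. One is contradicted, at two post-randomisation visits, and one is unclear.

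**Direction of any bias.** If testers shifted VO2max upward by the same amount in both trained arms, the shift would cancel in the low-versus-high comparison and remain in each comparison with control. An unequal shift would also affect the dose comparison. A constant shift by arm does not by itself produce a mediation path, because fitness must also relate to the outcome within arms. The documents give no value for such a shift.

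**The case against.** **The testers may be other people.** One section speaks of study physiotherapists and the other of the physiotherapists at the unit, and the blinded list contains a separate category of outcome assessors. A reader might infer that the staff who train a participant certainly also test that participant. The text does not say so, and the shared site settles nothing, since it covers all assessments. This part of the objection stands, so the fix must be conditional. It does not remove the conflict: no separate testers are described, and the Assessments section lists the physiotherapist alongside the blinded study staff.

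**An article condenses the full protocol.** That would excuse a missing detail. Here the article makes a positive claim that two of its other sections contradict.

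**The test is objective.** The Åstrand test is submaximal, the ergometer is calibrated and the value comes from a nomogram, so it depends less on effort and encouragement than a maximal test. This stands and limits how much bias to expect. The test is still administered and read by a person. The one-leg rise, with its requirements on control and speed, leaves more to judgement. A reader might therefore extend the finding to strength, but no tester is named, so only clarification can be asked for.

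**The outcome behind the sample size is untouched.** Correct: the sample size rests on BAI, which is self-reported. Nothing here shows that the anxiety result is compromised.

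**Conclusion.** The blinding claim is contradicted for one outcome, estimated VO2max, at 12 weeks and 1 year. This rests on reading the physiotherapist in the Assessments and Cardiovascular fitness sections as the role in the Blinding section. That is the natural reading, but it is not stated outright. For one-leg rises the status is unknown.

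The consequence is moderate. It concerns the physical-health part of the primary aim and the planned mediator or moderator analyses, not BAI or the M.I.N.I.

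Two stronger readings are not supported. A reader might put a false-positive rate on the fitness comparison. That needs an assumed tester shift with no anchor in the documents, and a true fitness effect of zero after 12 weeks of training. A reader might also conclude, from the physiotherapists carrying out the randomisation, that allocation was not concealed. That is a separate question, and the conflict described here does not answer it.

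**What to change.** 1. **Reconcile the Blinding, Assessments and Cardiovascular fitness sections.** State who runs the Åstrand test and the one-leg rise, and whether they know the allocation.
2. **If the testers are separate and blinded,** one sentence saying so closes the point.
3. **If they are not,** limit the blinding statement to the outcomes it covers. Report VO2max as measured by staff aware of allocation, and one-leg rises likewise if the same staff test them.
4. **For the remaining 12-week and 1-year tests,** use existing physiotherapists who did not train the participant and, where possible, do not know the allocation. Use a scripted test, record raw workload and heart rate, and have the blinded data collector apply the nomogram. A physiotherapist who did not train the participant may still know the group, so this reduces the problem without guaranteeing blinding, and the report should say so.

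The change is still practicable: recruitment is planned to March 2020, and the 1-year follow-up ends around June 2021.

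The cost is some scheduling effort, a less favourable blinding statement, and a testing procedure that differs between earlier and later trial sets. The report should state from which set the change applied. No new staff are needed.

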### Assessments

Assessments occur at baseline, post-intervention (after 12 weeks) and at one-year follow-up (Table 1). Participants will be assessed by the study physician, psychologist, psychiatrist and physiotherapist.

**Table 1 Tab1:** Measures, methods and assessment points used in the study

Variable	Measure	Method	T0 Baseline	T1 12 weeks	T2 1 year
Psychiatric diagnosis	M.I.N.I.	Interview	X	X	X
Anxiety symptoms	BAI	Self-report	X	X	X
Depression symptoms	MADRS	Self-report	X	X	X
Psychoactive drugs	Questionnaire	Self-report	X	X	X
Blood pressure	MmHg	Objective assessment	X	X	X
BMI	Kg/m^2^	Objective assessment	X	X	X
Alcohol use	AUDIT	Self-report	X	X	X
Quality of life	EQ-5D	Self-report	X	X	X
Cognitive function	WAIS-IV (d.s., b.d., m.r.)	Objective assessment	X	X	X
Cognitive function	D-KEFS (d.f.)	Objective assessment	X	X	X
Cardiovascular fitness	Åstrand’s ergometer test	Objective assessment	X	X	X
Muscle strength	One-leg-rising-test	Objective assessment	X	X	X
Sick leave	Questionnaire	Self-report	X	X	X
Hormones/cytokines	S-IGF-1, S-BDNF, S-VEGF, CRP	Blood samples	X	X	X

*M.I.N.I.* Mini International Neuropsychiatric Interview, *BAI* Beck Anxiety Inventory, *MADRS* Montgomery Åsberg Depression Rating Scale, *BMI* Body mass index, *AUDIT* Alcohol Use Disorders Identification Test, *EQ-5D* EuroQoL-5 Dimension Questionnaire, *WAIS-IV* Wechsler Adult Intelligence Scale, 4th edition, *d.s*. digit span, *b.d*. block design, *m.r.* matrix reasoning, *D-KEFS* Delis-Kaplan Executive Function System, *d.f*. design fluency, *S-IGF-1* serum insulin-like growth factor 1, *S-BDNF* serum brain-derived neurotrophic factor, *S-VEGF* serum vascular endothelial growth factor, *CRP* high sensitivity C-reactive protein

#### Mental health variables

Psychiatric diagnoses, determined by the study psychiatrist using M.I.N.I., are applied at initiation, at 12-weeks post-intervention and 1-year follow-up. Severity of perceived symptoms of anxiety and depression are assessed using the established psychiatric self-assessment scales Beck Anxiety Inventory (BAI) [31] and Montgomery Åsberg Depression Rating Scale (MADRS) [32]. Patients report use of psychoactive prescription drugs, including dosage and duration at each assessment.

#### Cognitive function

The Wechsler Adult Intelligence Scale, 4th edition (WAIS-IV) is used to measure executive functions and perceptual reasoning [33]. The *digit span forward*, *backward* and *sequencing* subtests were chosen to measure executive function, working memory, attention and mental manipulation. The *block design* and *matrix reasoning* subtests were chosen to measure visual-spatial processing and nonverbal problem-solving skills [33].

The Delis-Kaplan Executive Function System (D-KEFS) is a standardized, non-verbal psychomotor test battery assessing executive functions in individuals between 8 and 89 years old [34]. The subtest *Design fluency* resembles the cognitive chain required in daily life to generate novel responses, while maintaining focus on a desired goal, and measures processes such as creativity, response inhibition, and cognitive flexibility [34, 35]. The *Design fluency* subtest consists of three conditions, all performed using a pen and paper where the participant has to bind together dots and make as many novel shapes possible during 60 s. The participant needs to use working memory, inhibition and scanning skills to remember previously drawn shapes, inhibit the response to repeat shapes and scanning skills and creativity to find novel solutions to complete the assignment. The tasks appear in order of increasing difficulty, and the final trial includes a cognitive set-shifting component. D-KEFS has been used in both clinical and research settings showing good reliability and validity for measuring executive functions [35, 36].

#### Physical health variables

Blood pressure, weight and height are measured and body mass index (BMI) is calculated for each patient. Alcohol use is assessed using the Alcohol Use Disorders Identification Test (AUDIT) [37]. Patients self-report smoking, diet habits, concurrent illnesses, usage of prescribed drugs and physical activity in a questionnaire designed by the research team (Additional file 1). General health and perceived quality of life are measured using the EuroQoL-5 Dimension Questionnaire (EQ-5D), a standardized instrument measuring health related to five dimensions: mobility, self-care, usual activities, pain/discomfort and anxiety/depression [38].

#### Cardiovascular fitness

Maximal oxygen uptake capacity (VO2max) is estimated using Åstrand’s submaximal ergometer test and serves as a measure of cardiovascular fitness [39]. The test is performed by the physiotherapists at Primary Care Rehab. Participants are told to refrain from vigorous activity the day before the test, to avoid a heavy meal within three hours and smoking/snuff use one hour prior to the test and also to avoid stress during the test day. The ergometer is calibrated for each participant and heart rate is corrected for sex and age. Predicted VO2max is calculated in accordance with the nomogram described by Åstrand and Ryhming [39].

#### Muscle strength

Muscle strength is measured using a standardized test of maximum number of one-leg rises from sitting on a chair (45 cm high) during 1 min [40]. The patient is told to keep the arms crossed and to hold the other leg extended without touching the floor. The test is performed with full muscle control and at constant speed without adding arm or trunk movements.

#### Work ability

Patients self-report work ability, weekly number of work hours and if they are on sick-leave in a questionnaire (Additional file 2).

#### Blood samples

Blood samples are taken by a biomedical analyst to investigate any potential correlation of the following hormones/cytokines with anxiety symptoms and function data: S-insulin-like growth factor 1 (IGF-1), S-brain-derived neurotrophic factor (BDNF), S-vascular endothelial growth factor (VEGF) and high sensitivity C-reactive protein (CRP). Total accumulated blood volume is 15 ml per individual. The blood samples are coded and stored in a separate, locked freezer (− 70 degrees) at Sahlgrenska University Hospital, Gothenburg. All analyses will be performed in collaboration with the central laboratory at Sahlgrenska University Hospital, Gothenburg. After study completion, the samples will be destroyed. The Swedish Health and Social Care Inspectorate (IVO), a government agency under the Ministry of Health and Social Affairs, has been notified of the establishment of a biobank (No 946).

### Sample size calculation/power calculation

A power analysis was performed by a statistician prior to study initiation. We have calculated, based on other studies [41, 42], that an effect size of 0.5 difference between the groups is clinically relevant, which equates to a 5-point difference between the groups on the BAI scale. Standard deviations from a previous study using BAI as the outcome measurement were in the interval of 5–10 [43]. We use SD 9 for our calculations. Based on these assumptions, we should include 60 patients in each of the treatment arms to reach 80% power at the 5% significance level. In order to achieve an adequate number of study participants, we will initially recruit 25% more subjects than required.

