**Method/design:**

Using a parallel, RCT design with three assessment points (baseline, post-intervention and one-year follow-up), we aim to assess the effect of a 12-week exercise intervention in primary care patients with anxiety disorders (*n* = 180), diagnosed using the Mini International Neuropsychiatric Interview (M.I.N.I; Swedish version 6.0.0d DSM-IV). Participants are randomly assigned to three physical exercise groups: one low-intensity training group, one moderate- to high intensity training group and one control non-exercise group. Assessments include measures of anxiety symptoms, cognitive function, physical health variables such as cardiovascular fitness, sick-leave and levels of hormones/cytokines in blood samples.

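### Effect size 0.5, 5 BAI points and SD 9 cannot all hold, and 60 per arm at 80% power follows from neither reading (52 or 64 per arm)

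*Protocol article*

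**What the plan says.** All the design figures stand in the section on sample size and power of the protocol article.

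- Target effect: "an effect size of 0.5 difference between the groups is clinically relevant, which equates to a 5-point difference" on the BAI.
- Spread: "Standard deviations from a previous study using BAI as the outcome measurement were in the interval of 5–10", followed by "We use SD 9 for our calculations".
- Result, said to rest on these assumptions: "we should include 60 patients in each of the treatment arms to reach 80% power at the 5% significance level".
- Surplus: "we will initially recruit 25% more subjects than required".

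The only total in the article is in the abstract, which describes "patients with anxiety disorders (*n* = 180". The study design section gives three arms with 1:1:1 allocation. The statistical analysis section specifies ANCOVA with the baseline value as covariate. The article does not name the test behind the sample size, its sidedness, a drop-out rate or a baseline correlation.

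**The concern.** A standardised effect is the raw difference divided by the SD, so any two of the three design figures fix the third. Here all three are given and they disagree. The patient number said to follow from them should then match at least one of the possible pairs, and with the usual two-group calculation it matches none.

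This is the article's only justification of its size. As written, the target difference could be 4.5 or 5 points and the required number 52 or 64 per arm. If the trial ends without a clear difference, a reader will want to know which difference it was built to detect, and the text does not give one answer. Recruitment was planned to run until March 2020, after the article appeared in June 2019, so the recruitment target was still in use.

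**Working it through.** **Inputs.** From the sample-size section: d = 0.5, difference 5 points, SD 9, 60 per arm, power 80%, level 5%, surplus 25%. From the abstract: n = 180. Assumed, because not stated: a comparison of two arms, two-sided, by t-test without covariates.

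**Step 1. Do the inputs agree?** d = difference / SD.

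- 5 / 9 = 0.556, not 0.5.
- 0.5 × 9 = 4.5 points, not 5.
- 5 / 0.5 = 10, so equating 0.5 with 5 points needs SD 10, not 9.

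**Step 2. Does 60 per arm follow?** The normal approximation is n per arm = 2(1.960 + 0.842)² / d² = 15.70 / d². The exact t-test adds about one patient per arm.

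| Reading | d | n per arm, normal | n per arm, t-test | Power at 60, t-test |
|---|---|---|---|---|
| 5 points, SD 9 | 0.556 | 50.9, so 51 | 51.8, so 52 | 85.5% |
| d = 0.5 (4.5 points at SD 9, or 5 at SD 10) | 0.500 | 62.8, so 63 | 63.8, so 64 | 77.5% |

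By the normal approximation, power at 60 is 86.1% and 78.2%. Neither row reproduces 60 per arm at 80%.

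**Step 3. Can 60 be reached another way?**

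- One-sided 5%: 41 per arm (5 points, SD 9) or 51 (d = 0.5). No.
- Two-sided 2.5%, a Bonferroni split over two comparisons, with 5 points and SD 9: 63 per arm, and 77.9% at 60. Close, but not stated.
- 5 points with SD of about 9.7: 60 per arm. That SD lies within the cited interval of 5–10 but is not the SD the section says it used.
- Three-group F-test with d = 0.5 and both exercise arms equal: 59 per arm, and 80.8% at 60. Neither this test nor this pattern of means is stated. The article's additional hypothesis is that higher intensity has the larger effect. If the low-intensity arm is set halfway, the same F-test needs 79 per arm.

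**Step 4. The total.** Required: 3 × 60 = 180. With 25% more: 180 × 1.25 = 225, or 75 per arm. So 180 equals the required number, and 225 appears nowhere. If all 75 per arm were evaluable, power would be 92.2% (5 points, SD 9) or 86.0% (d = 0.5).

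**The case against.** Four points can be made for the plan, and most of them stand.

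1. **The slip may be harmless.** The section says that SD 9 was used. With 5 points, 60 per arm then gives 85.5%, above the stated 80%. This stands: on that reading the error is conservative.
2. **The shortfall on the other reading is small and may disappear.** It is 2.5 percentage points, and the planned analysis adjusts for baseline. The article gives no baseline correlation r. Assuming one and dividing d by √(1 − r²), 60 per arm at d = 0.5 gives 79.2% at r = 0.2, 81.3% at r = 0.3 and 88.0% at r = 0.5. Recruiting and retaining part of the surplus would also close the gap. This stands.
3. **The test is not named, so failure to reproduce 60 depends on the test chosen.** True, and the F-test in step 3 is a possible route. But it relies on a pattern of means that the text does not give, and it does not reconcile 0.5 with 5 points at SD 9.
4. **180 and the 25% surplus are compatible.** 180 can be the required number and about 225 the number recruited. This stands.

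A reader might go further and infer that the trial misses its stated power, or that the totals contradict each other. The article does not support either. The first fails by points 1 and 2. The second fails by point 4. A reader might also take 180 as already including the surplus, so that only 180 / 1.25 / 3 = 48 per arm would be required, with power of 76.8% or 67.9%. That runs against the wording, which gives 60 as the number needed and adds the 25% to what is required.

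**Conclusion.** The figures are wrong as written in two linked respects. The effect size, the point difference and the SD exclude each other. The stated 60 per arm at 80% does not follow from either consistent pair by a two-group, two-sided t-test: 52 or 64 per arm are needed, and 60 evaluable gives 85.5% or 77.5%. Values close to 60 arise only under assumptions that the text does not state.

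What this establishes is that the sample-size statement must be restated. It does not show that the trial is too small. The direction of the error depends on which effect was meant, and both power figures are before baseline adjustment. Separately, the article leaves open whether 180 is the required or the recruited number, a difference of 225 − 180 = 45 participants. These conclusions rest on the two-sided reading and on pairwise comparison of arms.

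**What to change.** Restate the calculation as one coherent set: the difference in points, the SD, the resulting d, the test and comparison it refers to, the sidedness, and the power that 60 evaluable per arm gives. Two forms would be consistent, by two-sided t-test at 5%:

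- 5 points with SD 9 (d = 0.56): 60 evaluable per arm gives about 85% power.
- d = 0.5 (4.5 points at SD 9, or 5 points at SD 10): 60 evaluable per arm gives about 78% power.

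Say that both are before baseline adjustment by ANCOVA. If a different calculation produced 60, such as a three-group F-test, name it with its assumed means.

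State whether 180 is before or after the 25% surplus, and use the same total in the abstract. Keep the surplus: a text that sets 180 as the number randomised would silently drop it and could lower recruitment from 225 to 180. Only the sponsor can say which was meant.

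The cost is wording only. No extra patients and no change of design are needed.
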